#### Missing data

Missing data might occur by patients’ withdrawal from trial, unreturned questionnaires after the consultation, or other circumstances. Reasons for withdrawal will be reported for each randomization group and compared qualitatively. The effect that any missing data might have on results will be assessed via sensitivity analysis of augmented data sets. Dropouts and item nonresponse will be included in the analysis by imputation methods for missing data. Missing values in the primary outcome (and in other outcomes) are replaced by multiple imputation. Through an iterative series of predictive models using the non-missing variables in the dataset, the imputation is conducted. The iterations are run until it appears that convergence has been met. The accuracy of the imputations will depend on the information density in the dataset. Diagnostic plots are used to determine how valid the imputations may be. Imputation is conducted via predictive mean matching (PMM). PMM involves selecting a datapoint from the original, non-missing data which has a predicted value close to the predicted value of the missing sample. The closest values are chosen as candidates, from which a value is chosen at random. After the imputations are completed, all of the data (complete and imputed) will be combined and the analysis performed for each imputed and completed dataset.

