### Criteria for discontinuing or modifying allocated interventions {11b}

Patients can leave the study at any time for any reason, without any consequences. If a patient’s health status declines and they are no longer able to answer the survey questions, they will be treated as a dropout. The same applies for participants who withdraw their consent for any other reason. Patient data collected up to that moment will not be included in the analysis.

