### Participant timeline {13}

Participation in the study includes the completion of two questionnaires for each participant (before and after the medical consultation at intervals of 1–4 weeks). The questionnaires will be handed over personally (including a stamped return envelope) or sent by e-mail. The time needed to answer the questionnaires is about 10 min.

In addition to the questionnaire survey, the application of the decision aid incl. decision coaching will be carried out with participants in the intervention group. This can take place, depending on the patient’s wishes, either in the clinic or at another location, by telephone or by video conference. The time frame is about 30–45 min for the decision aid and the accompanying conversation. Appointments are made in person, by phone, or by mail.

The total study-related time required is therefore about 20 min for persons who participate exclusively in the questionnaire survey and about 50 to a maximum of 65 min for persons who are invited both to the questionnaire survey and to the decision coaching (Figs. 1 and 2).

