### Sample size {14}

A clinically relevant difference of 10 points in the primary outcome between the two treatment groups was assumed to show a sufficient clinical difference for case planning. In addition, the standard deviation was estimated to be 20.6 from the literature [12]. Under these assumptions, *n*=71 patients per group are needed to demonstrate the assumed difference between the two groups at a two-sided significance level of 5% with a power of 80% using a Mann-Whitney *U* test. The calculation was performed by means of 100,000 simulation runs using the case number software PASS v 16.0.4. Taking into account a dropout rate of approx. 20%, 71/(1–0.20)=89 patients per group are included. These results in a total number of cases of *n*=178 patients are to be included in the study.

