**4) Sensitivity analyses**			
Per protocol analysis	Improvement in comparison to control	All outcomes	

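### Dropouts are imputed from patients who answered, and no described analysis tests whether those lost to worsening health would have scored worse; the rule on dropouts' data also contradicts the intention-to-treat definition

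*Protocol article*

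**What the plan says.** Protocol article, Criteria for discontinuing or modifying allocated interventions {11b}: when health declines so far that "they are no longer able to answer the survey questions, they will be treated as a dropout". The same paragraph then says that data gathered before dropout are left out of the analysis.

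Protocol article, Analysis population {20c}: the intention-to-treat population is everyone as randomized, whether or not they completed the survey. The per-protocol population is limited to patients who stayed in their group and answered both questionnaires in time.

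Protocol article, Missing data {20c}: dropouts and item nonresponse enter the analysis through multiple imputation, for the primary and other outcomes. The method is predictive mean matching, described as "selecting a datapoint from the original, non-missing data which has a predicted value close to the predicted value of the missing sample". The stated check is that "The effect that any missing data might have on results will be assessed via sensitivity analysis of augmented data sets". Reasons for withdrawal are to be reported and compared qualitatively by group.

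Protocol article, Table 2, block 4: the only sensitivity analysis listed is "Per protocol analysis", for all outcomes.

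**The concern.** In advanced lung cancer, being too ill to answer is plausibly related to the score the patient would have given. Predictive mean matching cannot reflect this beyond what the observed variables carry, because every donor was well enough to respond. Those variables may be thin for the primary outcome. The text describes no Decisional Conflict Scale measurement before the intervention, so a patient lost before the first questionnaire has no earlier score to inform the imputation.

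The assumption is acceptable for a main analysis if something else tests it. The article states that aim, but neither of the two analyses it names departs from the assumption.

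There are also design reasons why losses might differ by arm. Controls spend about 20 minutes on the study, against "about 50 to a maximum of 65 min for persons who are invited both to the questionnaire survey and to the decision coaching". Under Implementation {16c}, controls get their questionnaires at allocation, while intervention patients get theirs only after arranging and attending coaching. If intervention losses were larger or sicker, imputing them as responders would favour HELP, and the described analyses would not be built to detect it.

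**Working it through.** **1. The plan's own figure.** The inputs all come from the section headed Sample size {14}. Target, in the article's words: "A clinically relevant difference of 10 points in the primary outcome between the two treatment groups was assumed to show a sufficient clinical difference". Spread, taken from an earlier study: "the standard deviation was estimated to be 20.6 from the literature". Error rates and test: "two-sided significance level of 5% with a power of 80% using a Mann-Whitney".

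- Normal approximation: 2 × (20.6 × (1.96 + 0.8416) / 10)² = 66.6, so 67 per group.
- Divided by the Mann-Whitney efficiency 3/π: 70 per group.
- Simulated Mann-Whitney power (40,000 runs, normal data): 0.796 at 70 and 0.802 at 71. The stated 71 reproduces.
- 71 / (1 − 0.20) = 88.75, so 89 per group and 178 in total. This also reproduces.

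The sample size is not in question. The 20% loss is, however, applied to the number needed for the primary outcome, so the plan itself allows for primary scores being missing on that scale.

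**2. Bias in the group difference.** Let p be the dropout proportion in each arm (I = intervention, C = control), and δ the amount by which dropouts score worse than the values imputed for them. Then

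bias = p_I × δ_I − p_C × δ_C.

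The documents give only about 20% dropout overall. The split by arm and δ are assumptions. With the same δ in both arms, applied to every dropout:

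| Dropout I / C | δ = 10 | δ = 20.6 (1 SD) |
|---|---|---|
| 20% / 20% | 0 | 0 |
| 25% / 15% | 0.10 × 10 = 1.0 | 0.10 × 20.6 = 2.06 |
| 30% / 10% | 0.20 × 10 = 2.0 | 0.20 × 20.6 = 4.12 |

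This is roughly 10% to 40% of the 10-point target. If only half the dropouts in each arm carry the shift, the range halves to 0.5 to 2.06 points. If the control arm loses more patients, the sign reverses and HELP's benefit is understated.

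Rates may also be equal while shifts differ. With 20% dropout per arm, an observed difference of 10, and only intervention dropouts worse by 10 or 20.6, the difference over all randomized patients is 10 − 0.20 × 10 = 8.0 or 10 − 0.20 × 20.6 = 5.9.

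**3. Type I error, no true difference over all randomized patients.** Mann-Whitney on responders, 89 per arm, 20,000 runs, same shift in both arms:

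| Dropout I / C | δ = 10 | δ = 20.6 |
|---|---|---|
| 20% / 20% | 0.048 | 0.050 |
| 25% / 15% | 0.062 | 0.088 |
| 30% / 10% | 0.086 | 0.209 |

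**4. Does imputation from responders miss the shift, and does a delta adjustment recover it?** A simplified version of the planned imputation was simulated: donors drawn within arm and stratum, 10 imputations, van Elteren test, 300 runs, 20% dropout per arm, shift in intervention dropouts only.

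- Shift 10: full-data difference 8.2, imputed estimate 10.0.
- Shift 20.6: full-data difference 6.0, imputed estimate 10.2.
- In runs with a delta adjustment of the same size: imputed 8.4 against full-data 8.3, and 5.8 against 5.8.

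**5. Where a result would tip.** With an observed difference of 10, the standard error is 20.6 × √(2/71) = 3.46, and the smallest significant difference is 1.96 × 3.46 = 6.78. The intervention-only shift that removes significance is (10 − 6.78) / p_I: about 16 points at 20% dropout, 13 at 25% and 11 at 30%, keeping the same standard error throughout.

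**6. The sections side by side.** {11b} removes dropouts' data. Analysis population keeps all randomized patients. Missing data imputes dropouts. The first cannot hold together with the other two. If {11b} governs, the analysis uses responders only, and dropout that is not at random is still untested.

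**The case against.** The case against has real substance.

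- **The key term is undefined.** A reader might infer that the sensitivity analysis certainly reuses the same imputed data. The article does not say so. Imputation is the only augmentation it describes, which makes this the natural reading, but a full protocol or analysis plan could define the term otherwise. This stands.
- **The other checks are not empty.** A reader might infer that the plan cannot show anything about dropout, or that every check would agree with the main result. Withdrawal reasons by arm, and a comparison of imputed with per-protocol results, give some information. None of it addresses dropout that is not at random. The absolute wording fails; the narrower point stands.
- **It is not certain that these patients are imputed.** {11b} points the other way, so the contradiction belongs to the point.
- **The window before the primary outcome looks short.** The Fig. 1 legend puts enrolment-stage time points 6–8 days and the next ones 2–5 days before the consultation, which suggests about a week or less for health to remove the score (the figure itself is not shown). Patients whose vital threat prevents conversation are excluded. Questionnaires not returned after the consultation affect the Patient Involvement in Care Scale and the second EQ-5D and HADS, not the primary outcome, and EQ-5D and HADS have an earlier value. This tempers the likely size, although the plan's own 20% allowance applies to the primary outcome.
- **The magnitudes are assumed.** Nothing in the documents shows that frailer patients have less values clarity. An extra 30–45 minutes, available by telephone or video, does not establish a 10 to 20 percentage-point excess in dropout. A reader might infer that the trial is biased towards HELP; the documents do not support that.

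**Conclusion.** The point holds in a limited form. As described, the main analysis assumes that dropouts resemble responders with the same observed data. One named dropout reason makes that assumption doubtful, and no described analysis departs from it, although the article sets out to assess the effect of missing data. Leaving mechanics to an analysis plan does not fully answer this, because the article itself fixes the imputation method, states the purpose of the check and lists its sensitivity analyses.

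The 1.0 to 4.1 point range is an illustration. It requires unequal dropout between arms and a shift of 0.5 to 1 SD in every dropout, and it is zero when rates and shifts are equal. Multiple imputation remains a sound main analysis and the sample size is unaffected. Separately, the conflict over dropouts' data is a plain contradiction in the text and has to be settled before any sensitivity analysis can be run.

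**What to change.** 1. Reconcile {11b} with Analysis population and Missing data so that all randomized patients are analysed as the intention-to-treat definition states, subject to consent for use of data already collected.
2. Keep multiple imputation by predictive mean matching as the main handling.
3. Replace the undefined sensitivity analysis of augmented data sets with a delta-adjusted (tipping-point) analysis of the primary outcome, and of EQ-5D and HADS. Worsen the imputed values of patients lost to health decline in steps from 0 to about 1 SD, separately by arm, and report the shift at which the conclusion changes. Identify these patients from the withdrawal reasons that are already to be recorded.
4. Add this analysis to the sensitivity block of Table 2.

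The cost is a small amount of programming on imputed data sets that will exist anyway, one table row and some extra reporting. No new data are needed, and the primary test does not change.

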#### Control group

The participants in the control group get usual care, i.e., the doctor-patient conversation takes place without preliminary coaching and deliberation about their preferences and goals.

Before the consultation with their physician, participants fill in the pre-survey questionnaires (Decisional Conflict Scale, Decision Self-Efficacy Scale, EQ 5D, Hospital Anxiety and Depression Scale). After the consultation, the post-survey questionnaires are handed out or mailed to them (Patient Involvement in Care Scale, EQ-5D, Hospital Anxiety and Depression Scale).

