## Assignment of interventions: allocation

### Sequence generation {16a}

Randomization to the two groups of the study (control and intervention group) will be performed in a ratio of 1:1. Stratified block randomization will be performed according to the characteristic of preferred decision-making at baseline (expressions: physician should decide; patient would like to decide alone; patient and physician should decide together). This is to ensure that participants are evenly distributed within the study groups according to their preferred decision style, since it is assumed that the intervention effect differs according to the individual differences in preferences for decision style.

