### Methods in analysis to handle protocol non-adherence and any statistical methods to handle missing data {20c}

#### Analysis population

As analysis populations, the two common populations of intention-to-treat and per-protocol are defined and used. The intention-to-treat population considers all patients as randomized regardless of whether they finished the whole survey procedure. Criteria for determining the per-protocol population are as follows: patients who stayed in their randomized group, answered the first questionnaire before the decision-making (and for IG: after the intervention), and answered the second questionnaire within the timeframe of 1–4 weeks after the treatment decision.

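### The imputation rule conflicts with the dropout rule and, if followed, fills in post-consultation scores that are undefined rather than missing

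*Protocol article*

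**What the plan says.** Three parts of the protocol article bear on patients who do not complete the study.

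- **Missing data (item 20c).** Dropouts and unanswered items enter the analysis by imputation, and "Missing values in the primary outcome (and in other outcomes) are replaced by multiple imputation". The method is predictive mean matching. No outcome and no kind of patient is excepted.
- **Analysis population (item 20c).** "The intention-to-treat population considers all patients as randomized regardless of whether they finished the whole survey procedure".
- **Criteria for discontinuing (item 11b).** "If a patient’s health status declines and they are no longer able to answer the survey questions, they will be treated as a dropout". Patients who withdraw consent are treated in the same way, and the item closes by leaving out of the analysis whatever these patients had supplied before that point.

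On timing, the Control group section says "After the consultation, the post-survey questionnaires are handed out or mailed to them (Patient Involvement in Care Scale, EQ-5D, Hospital Anxiety and Depression Scale"); the intervention group receives the same three scales after the consultation. The legend of Figure 1 places enrolment and allocation 6 to 8 days before the consultation and the last assessment (t4) 1 to 14 days after it. The Trial design section places the primary outcome before the decision event. Neither death nor a consultation that fails to take place is mentioned anywhere in the article.

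**The concern.** PICS asks how the physician and the patient behaved in the consultation. A patient who never had that consultation has no PICS value to estimate, and a patient who has died has no quality of life or anxiety score at t4. Imputation is meant for values that exist but were not observed. A rule that imputes every outcome for every dropout does not make that distinction.

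At stake is the meaning of the post-consultation comparisons. Involvement in the decision is a stated secondary objective, and an unknown part of the PICS data could describe consultations that did not happen. The conflict with item 11b adds a second difficulty: two analysts working from this article could treat the same dropout in opposite ways.

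**Working it through.** **Planned numbers.** The inputs from Sample size (item 14) are "A clinically relevant difference of 10 points in the primary outcome", "the standard deviation was estimated to be 20.6 from the literature", and a "two-sided significance level of 5% with a power of 80" per cent, with a Mann-Whitney test. From item 16a: "Randomization to the two groups of the study (control and intervention group) will be performed in a ratio of 1:1".

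- Normal approximation: n = 2 × [20.6 × (1.960 + 0.842) / 10]² = 66.6, so 67 per group.
- Divided by the Mann-Whitney efficiency 3/π = 0.955: 69.8, so 70 per group.
- Simulated Mann-Whitney test on normal data, 20,000 runs: power 79.5% at 70 and 80.1% at 71 per group. The plan's 71 is reproduced.
- Dropout inflation: 71 / (1 − 0.20) = 88.75, so 89 per group and 2 × 89 = 178 in total. Both are reproduced.

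**The rules side by side.**

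| Situation | PICS | EQ-5D, HADS at t4 | Item 20c | Item 11b |
|---|---|---|---|---|
| Consultation held, alive, form not returned | exists, missing | exist, missing | imputed | data left out if too ill to answer or withdrawn |
| Alive, no consultation | undefined | defined as a state of the patient | imputed | data left out if too ill to answer or withdrawn |
| Consultation held, died before t4 | consultation took place, not rated | undefined | imputed | death not named |
| Died before the consultation | undefined | undefined | imputed | death not named |

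In the first row imputation is reasonable. In the other rows, item 20c as written fills at least one cell that has no true value. Where item 11b applies, the two items give opposite instructions.

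**Time at risk.** From enrolment to t4: 6 + 1 = 7 days at the shortest and 8 + 14 = 22 days at the longest. With the 1 to 4 week window of the per-protocol definition, the longest is 8 + 28 = 36 days.

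**Scale.** Expected dropouts: 0.20 × 178 = 35.6, about 36 (0.20 × 89 = 17.8, about 18 per arm). The article does not say what share of dropouts would have had no consultation or have died. Taking that share as an assumption:

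| Assumed share of dropouts | Patients | Share of the 178 |
|---|---|---|
| 0% | 0 | 0% |
| 10% | 3.6, about 4 | 2% |
| 25% | 8.9, about 9 | 5% |
| 50% | 17.8, about 18 | 10% |
| 100% | 35.6, about 36 | 20% |

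**Outcomes touched.** Table 2 lists 11 secondary between-group comparisons. Three are PICS subscores. EQ-5D and HADS add two, to the extent that they are analysed at t4, since both are also collected before the consultation. That is at most 5 of 11. The sample size rests on the primary outcome and does not change.

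**The case against.** The other side has several good points.

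- **The rule is not settled.** A reader might infer that every dropout will be given invented ratings. Item 11b does not allow that conclusion, because on its terms the data of patients too ill to answer are not analysed at all. What stands is the conflict, and the consequence if item 20c prevails.
- **The events are inferred.** The article's own example of missing post-consultation data is a form not returned after a consultation that did take place. The window is short, and the eligibility criteria exclude patients whose condition rules out conversation because of a vital threat. The true number may be near zero. The 20% is also the planning figure behind the sample size for the pre-consultation primary outcome, so applying it to t4 is a further assumption.
- **EQ-5D and HADS.** A reader might infer that these results would describe a cohort in which nobody dies or deteriorates. That goes too far. Both scales are defined for a living patient without a consultation, and scores returned before the consultation can inform the imputation. The argument covers them only after death.
- **The primary outcome.** The quoted sentence names it first, so a reader might infer that it is compromised. It is collected before the consultation, and this argument does not reach it.
- **Planned safeguards.** Withdrawal reasons are to be tabulated by arm, a sensitivity analysis for missing data is planned, and a per-protocol analysis requires an answered second questionnaire. So it is not right to say that the plan would simply hide a difference between arms. These measures still do not repair the main rule. The per-protocol analysis is only a sensitivity analysis and also removes living patients who had the consultation but did not return the form. Withdrawal reasons need not identify deaths or missed consultations.
- **Detail for another document.** Handling of death is often left to the analysis plan. Here, however, the article states a rule that covers all outcomes, and that rule contradicts another of its sections.

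**Conclusion.** The point holds in limited form. Item 11b and the two parts of item 20c cannot both be applied to the same dropout. If item 20c is followed, it yields PICS scores for consultations that did not take place and t4 EQ-5D and HADS scores for patients who have died, and neither has a true value.

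The size is unknown: from no patients up to some share of about 36, assuming that the planned 20% dropout also applies at t4. No figure in the article narrows that range, and the short window argues for the lower end. The undefined values arise in secondary outcomes only. The correction is still worth making, because the present rule is wrong for these patients and limiting it takes a few sentences.

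**What to change.** 1. Reconcile item 11b with item 20c so that data collected before dropout are kept in the analysis, including questionnaires returned before the consultation. If withdrawal of consent to data use is to be handled differently, say so as a separate case.
2. In the Missing data section, restrict imputation of PICS to patients whose consultation took place, and imputation of t4 EQ-5D and HADS to patients alive at t4. Imputation remains for living patients who had the consultation and did not return the form.
3. Record for each randomised patient the consultation date (or that none took place) and vital status at t4. Report the numbers with no consultation and with death before t4 by arm, beside the t4 results.

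The cost is wording plus two data items that a single-centre trial should be able to obtain from clinic records. The sample size and the primary analysis method are unchanged. The downside is real: the secondary comparisons lose a few patients and then condition on having had the consultation or being alive. Both are events after randomisation. If they differ between arms, the comparison is no longer fully protected by randomisation, so the by-arm counts must be read with it.
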